### 2.21. Outliers

Outliers are extreme values that are well outside the overall pattern of a distribution of variables leading to under- or overestimation of the true mean. A potentially important source of bias, it is important to consider in advance how these will be managed in the analysis of the data set [23]. To identify outliers, we will use box plots. Box plots are considered most suitable for exploring both symmetric and skewed data. Infrequent values in categorical data can also be identified using the box plot [23].

There are two main procedures for managing outliers: First, we will go back to the data and check the original value entered. If the extracted number is incorrect, we will amend our database accordingly, documenting any changes that have been made. Second, if the source and extracted data match but the value is seemingly impossible (e.g., the participant was 150 years of age), we will delete the data and consider the value as missing in the analysis.

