### 2.10. Patient-Level Data

From the relevant electronic patient records, we will extract and code (details of how we will code in parentheses) the following variables: Age (age in years at point of hospital admission), gender (coded: 1. Male, 2. Female, 3. Other), employment status at the point of admission (coded: 1. Employed, 2. Unemployed, 3. Student, 4. Retired, 5. Other), primary psychiatric diagnosis (coded: 1. Mood and/or anxiety disorder [including bipolar], 2. Schizophrenia, 3. Personality disorders, 4. Other [specify]), psychiatric comorbidities (coded: 1. Yes, 2. No), substance use (coded: 1. Yes, 2. No), physical comorbidities (coded: 1. Yes, 2. No), date of admission (dd/mm/20yy), detained under mental health law (coded: 1. Yes, 2. No), on a Community Treatment Order prior to admission to hospital (coded: 1. Yes, 2. No), when was the patient discharged from the participating ward? (dd/mm/20yy), Discharged on a Community Treatment Order (coded: 1. Yes, 2. No), admitted by inpatient psychiatric services at the participating hospitals within 12 months of discharge (coded: 1. Yes, 2. No), number of psychiatric admissions during the study period, Health of the National Outcome Scales (HoNOS) total score on admission to hospital, HoNOS total score immediately prior to discharge (recorded as number). Health of the Nation Outcome Scales (HoNOS) is a clinician rated tool comprising 12 simple scales assessing behaviour, impairment, symptoms and social functioning for those in the 18–64 years old age group [20]. We will request the unit managers to extract information on the total number of inpatients on the ward at morning handover (07:00 am) each day between the 6 January 2020 and 5 March 2020 (60 days). The patient data extraction form is available as Supplementary Document (Table S2).

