### 2.18. Data Recoding

Data will be recoded using the following procedure: A codebook will be created that will contain variable names and numeric codes. A number will be assigned to the label for each variable, for example, for gender, male will be coded 1 and female 2, other 3.

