### 2.23. Management of Missing Data

We will determine if there is a pattern to missing values, are data missing at random or is there a systematic reason for the missingness of data, i.e., missingness depends at least in part on unobserved variables [26].

We will use Little’s MCAR test to assess if data are missing completely at random (MCAR). The data will be assumed to be MCAR if the *p*-value for Little’s MCAR test is not significant. If data are not MCAR, we will conduct further exploratory tests to determine missingness at random (for example, the significance tests of missingness). The significance tests of missingness will determine if data are missing at random (MAR) or missing not at random (MNAR) [26].

The key variables in this study are readmission and the educational preparation of nurses. A listwise deletion method will be used where data are missing completely at random, and the missing data include either of the two key variables. The use of listwise deletion, in this case, is appropriate because data for patients with no outcomes and data for nurses missing educational preparation cannot be analysed to give the association between patient outcomes and educational preparation of nurses.

We will use the pairwise deletion method where data will be missing completely at random and do not involve key variables (i.e., readmission). This will enable us to retain data and minimise the potential for selection bias.

If data are MAR, multiple imputations will be used using three steps: Imputation, completed-data analysis (estimation), and pooling step [27]. We will use listwise deletion if data are MNAR since there is no acceptable remedy for it [26].

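### Section 2.21 relies on box plots to find infrequent categorical values, but on arbitrary number codes a box plot flags numeric distance, not rarity

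*Protocol article*

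**What the plan says.** Section 2.21 (Outliers) of the protocol article names one detection tool: "To identify outliers, we will use box plots". It then extends that tool to categorical fields: "Infrequent values in categorical data can also be identified using the box plot". Two actions follow. The value is first compared with source: "If the extracted number is incorrect, we will amend our database accordingly, documenting any changes that have been made". A value that matches source is deleted and treated as missing only if it looks impossible.

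The categorical fields are numbers by design. Section 2.18 says: "A codebook will be created that will contain variable names and numeric codes", and gives gender as its example ("for gender, male will be coded 1 and female 2, other 3"). Section 2.10 codes employment 1 to 5, primary diagnosis 1 to 4, and several Yes/No fields 1 or 2, among them readmission within 12 months. Section 2.12 codes nurse training 1 to 5. Section 2.23 states: "The key variables in this study are readmission and the educational preparation of nurses". Both key variables are therefore held as category codes.

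**The concern.** A box plot orders values on a numeric scale and marks those far from the middle half of the data. That makes sense for age or length of stay. For a nominal field the scale is only the order in which labels were numbered, so a category is flagged or passed because of its number and not because it is infrequent. The stated purpose, finding infrequent values, is not reliably served. A rare code or one outside the codebook can pass while a commoner end code is flagged.

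The flag has a consequence, because flagged values are checked against source and corrected. The rule therefore helps decide which records are verified. In a Yes/No field that choice can follow the recorded value itself, and readmission is such a field.

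**Working it through.** The protocol gives no figure to reproduce on this point. The check applies the box-plot rule to the protocol's own codes.

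**Inputs.** Codes are from sections 2.10, 2.12 and 2.18. The fence is assumed to be the standard one, since section 2.21 states none: lower = Q1 - 1.5 x IQR, upper = Q3 + 1.5 x IQR, with IQR = Q3 - Q1. Category mixes are assumptions for 100 records. The protocol gives none.

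**1. Yes/No field coded 1 = Yes, 2 = No (readmission).**

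| Yes (%) | Q1 | Q3 | Fences | Flagged |
|---|---|---|---|---|
| 5, 15, 20, 24 | 2 | 2 | 2 to 2 | every Yes, no No |
| 26, 50, 74 | 1 | 2 | -0.5 to 3.5 | none |
| 76, 85 | 1 | 1 | 1 to 1 | every No, no Yes |

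In the middle row, 1 - 1.5 x 1 = -0.5 and 2 + 1.5 x 1 = 3.5. At exactly 25% or 75% the result depends on how quartiles are defined. The Stata percentile definition and linear interpolation agree elsewhere in the table.

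**2. Multi-level fields.**

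- Diagnosis at 40/40/5/15%: Q1 = 1, Q3 = 2, fences -0.5 to 3.5. Code 4 (15%) is flagged and code 3 (5%) is not.
- The same 1% category under different numbers: coded 4 (40/40/19/1%), the fences are -0.5 to 3.5 and it is flagged. Coded 1 (1/40/19/40%), Q1 = 2 and Q3 = 4, the fences are 2 - 3 = -1 and 4 + 3 = 7, and it is not flagged.
- Nurse training at 4/56/25/5/10%: Q1 = 2, Q3 = 3, fences 0.5 to 4.5. Student nurses (code 5, 10%) are flagged. Mental health nurses (code 1, 4%) and nursing assistants (code 4, 5%) are not.

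**3. Rare and invalid codes.** Gender at 50/48/2%: fences -0.5 to 3.5, so the 2% category coded 3 passes, and so does an invalid 0. An invalid 4 is flagged. In a Yes/No field with 40% Yes, invalid codes 0 and 3 pass while 4 and 9 are flagged. Where IQR = 0, every code other than the dominant one is flagged, however common it is. The rule can miss such codes; it does not always miss them.

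**4. What one-sided checking could do to the readmission proportion.** Let t be the true proportion, m the share of true readmissions recorded as No, and f the share of true non-readmissions recorded as Yes. Before checking, observed = t(1 - m) + (1 - t)f. If this is under 25%, every Yes is verified and no No is. If the check finds every false Yes, t(1 - m) remains. Take t = 0.20; all rates are assumed.

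- m = 0.10, f = 0.02: before, 0.18 + 0.016 = 19.6%; after, 18.0%. The error grows from 0.4 to 2.0 points.
- m = 0.05, f = 0.05: before, 0.19 + 0.04 = 23.0%; after, 19.0%. The error shrinks from 3.0 points to 1.0 point.

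The check lowers the figure in both cases, but it moves away from the truth in one and closer in the other.

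**The case against.** The strongest reply is that section 2.21 is mainly about continuous data. It describes outliers as values that distort a mean, and its example of an impossible value is an age. The categorical sentence says what a box plot can do. Nowhere does the section say that readmission, or any Yes/No field, will be box-plotted. That stands, so the consequence for readmission is conditional on the sentence being applied to that field.

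A reader might go further and infer that the plan biases readmission downward. The documents do not support this. They give no 12-month rate for this population; the only figure, in section 1.5, is more than 15% within 30 days in schizophrenia. They give no error rates. Between 25% and 75% readmitted the rule flags nothing in this field, and above 75% it flags only No. One of the two scenarios above also ends nearer the truth.

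Other sections give partial cover. Section 2.22 looks for typing errors in categorical values, and section 2.24 reports numbers and proportions, so an out-of-codebook code might be noticed there. Neither section names a comparison of codes with the codebook, and neither changes which values section 2.21 sends to source. A condensed article may leave code-range checks to a fuller document, but the point here is a method that the article states and that does not work as described.

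Finally, section 2.26 rules out inference and the aim is feasibility. That limits the consequence to data quality and a descriptive proportion.

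**Conclusion.** The categorical sentence in section 2.21 is wrong as written. On arbitrary codes, a box plot with the usual fence flags by distance from the quartiles. It can pass rare or invalid codes while flagging commoner ones. In Yes/No fields it flags only a level held by fewer than 25% of records, and nothing when both levels exceed 25%. This rests on the 1.5 x IQR fence and on plotting the numeric codes; the category mixes are illustrative.

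If the rule is applied to readmission, source checking would depend on the recorded outcome: only Yes below 25% readmitted, only No above 75%, none in between. Neither the direction nor the size of any effect on the readmission proportion can be established from the protocol. This is a minor point for a descriptive feasibility study, but it is worth correcting because the study is meant to inform the methods of a larger one.

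**What to change.** In section 2.21, delete the sentence on categorical data and limit box plots to continuous and count fields: age, length of stay, HoNOS scores and daily counts.

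For coded fields, tabulate every code against the codebook already planned in section 2.18, and query any code that is not in it.

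State that the recorded readmission value alone does not trigger a source check. Trigger checks by invalid codes or by conflict with admission and discharge dates, applied equally to Yes and No. A readmission of No with more than one admission in the study period should prompt a check of dates and not count as an error in itself. The period runs from 6 January 2020 to 5 March 2021, so a patient discharged on 10 January 2020 and readmitted in February 2021 is correctly No with two admissions.

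The cost is a change of wording and a few lines of Stata for tabulation and date checks, with no new data. The downside is a slightly different set of records to query, possibly including some No records that the box plot would not have flagged.

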### 2.22. Data Consistency

Categorical variables and values will be checked for typing errors and inconsistent capitalization, for example, in gender, male can be entered as male in some participants and in some as male or m-ale. Inconsistent values can cause unnecessary delays during the analysis [22,23,24,25]. We will also check that dates are recorded in a consistent way (i.e., day, month, year and not month, day, year).

### 2.23. Management of Missing Data

We will determine if there is a pattern to missing values, are data missing at random or is there a systematic reason for the missingness of data, i.e., missingness depends at least in part on unobserved variables [26].

We will use Little’s MCAR test to assess if data are missing completely at random (MCAR). The data will be assumed to be MCAR if the *p*-value for Little’s MCAR test is not significant. If data are not MCAR, we will conduct further exploratory tests to determine missingness at random (for example, the significance tests of missingness). The significance tests of missingness will determine if data are missing at random (MAR) or missing not at random (MNAR) [26].

The key variables in this study are readmission and the educational preparation of nurses. A listwise deletion method will be used where data are missing completely at random, and the missing data include either of the two key variables. The use of listwise deletion, in this case, is appropriate because data for patients with no outcomes and data for nurses missing educational preparation cannot be analysed to give the association between patient outcomes and educational preparation of nurses.

We will use the pairwise deletion method where data will be missing completely at random and do not involve key variables (i.e., readmission). This will enable us to retain data and minimise the potential for selection bias.

If data are MAR, multiple imputations will be used using three steps: Imputation, completed-data analysis (estimation), and pooling step [27]. We will use listwise deletion if data are MNAR since there is no acceptable remedy for it [26].

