### 2.12. Nurse-Level Data

#### Roster Data

Roster data will be extracted from CHRIS21 and Kronos for the time period 6 January 2020 through 5 March 2020. System Performance Support [21] defined a roster as a timetable that specifies the number of nurses and their classifications required for each shift. Data on the training nurses have received will be extracted and coded: 1. Mental health nurse, 2. Comprehensive nurse, 3. Enrolled nurse, 4. Nursing assistant, 5. Student nurse. Nurse unit managers will be asked to extract and code data from the shift roster about whether nurses have mental health nursing qualifications. We estimate that data extraction and coding should take no more than four hours of a nurse unit manager’s (NUMs) time. We will check with NUMs during the conduct of the study if the tasks were overly burdensome. We defined a mental health nurse as a registered nurse with a formal educational qualification in mental health nursing. A comprehensive nurse is a registered nurse with a formal educational qualification in general/comprehensive nursing and does not hold a formal mental health nursing qualification. An enrolled nurse is a nurse with a certificate or diploma qualification in nursing and is registered as an enrolled nurse. First level nurse refers to mental health and comprehensive nurses. Second level nurses are enrolled nurses. These data will be entered onto a data extraction form available as Supplementary Document (Table S3).

We will use the total number of nurses working each day as the denominator and then calculate the ratio of 1. Mental health nurse to comprehensive nurse, 2. Registered nurse to enrolled nurse, 3. Qualified nurse to unqualified staff.

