### 2.25. Calculating Nursing Skill Mix

Each patient will have an individual row in the dataset. For each day (07:00 to 06:59) that the patient is in hospital, we will calculate the total number of registered nurses, unqualified nurses, mental health nurses, comprehensive nurses, enrolled nurses, student nurses, nursing assistants, and total number of patients on the ward. We will use these data to compute the following skill mix ratios on a day-by-day basis:○Mental health nurse to comprehensive nurse.○Qualified nurse to nursing assistant.○All nurse (including nursing assistant) to patient.○Mental health nurse to patient.○Comprehensive nurse to patient.

To compute the final skill mix measure, we will calculate averages for the duration of their admission, using days of admission as the denominator. For example, to calculate the comprehensive nurse to mental health nurse ratio. we would perform the following calculation. A patient was in hospital for three days. On the first day, there were eight comprehensive and two mental health nurses who provided care. On the second and third days, respectively, there were nine and ten comprehensive and three and four mental health nurses. This would give us a skill mix ratio of comprehensive to mental health nurses of 3:1.

To calculate nursing hours per patient day, we will total the number of nurses working on a given day, multiply by seven days and then divide by the number of patients on the ward at midnight.

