### Limitations

We have not tested the validity and reliability of routine hospital data collection, which is common in this type of research. Routinely collected health data in research studies are accepted as valid and reliable in Australia and worldwide. For example, in the United Kingdom, routine primary care data have been used in research for almost 30 years [28]. Still, the accuracy of the data has never been checked. Hospitals do not collect data on agency nurses’ educational preparation, which may affect the precision of our skill mix estimates. Nursing hours per patient day estimate the total amount of care time available. Likely, it is an overestimate of the actual amount of bedside nursing care patients receive.

We proposed extracting nurse data on gender, age, years of experience, and the type of contract (full-time or part-time), however, the human research ethics committee advised that these data were not required to achieve the aims of the study. It may be important to collect these data in future studies where it will be necessary to adjust for confounding in any proposed analysis. COVID-19-related data, such as isolation, vaccination status, or infections, which could be confounding factors, will not be retrieved. We anticipate that data on COVID-19 would be difficult to obtain.

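### Listwise deletion for unknown nurse education, which hospitals do not hold for agency nurses, would understate total staffing or lose patients, and the skill-mix ratio has no bounds

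*Protocol article*

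**What the plan says.** All references are to the protocol article.

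- **Who is counted.** Section 2.4 includes all first and second level nurses, assistants and students on the units across all shifts. Agency nurses are not excluded.
- **How education is coded.** Section 2.12 gives five codes: "1. Mental health nurse, 2. Comprehensive nurse, 3. Enrolled nurse, 4. Nursing assistant, 5. Student nurse". None stands for unknown.
- **What is known to be missing.** The Limitations state "Hospitals do not collect data on agency nurses" with respect to educational preparation, and describe the consequence as one for precision.
- **How missing education is handled.** Section 2.23 states "The key variables in this study are readmission and the educational preparation of nurses". It then sets three branches:
  - Missing completely at random: "A listwise deletion method will be used where data are missing completely at random, and the missing data include either of the two key variables".
  - Missing at random: "If data are MAR, multiple imputations will be used using three steps".
  - Missing not at random: "We will use listwise deletion if data are MNAR since there is no acceptable remedy for it".
- **Why.** The reason for deletion is that "data for patients with no outcomes and data for nurses missing educational preparation cannot be analysed" to estimate the association between education and outcome.
- **What is computed.** Section 2.25 lists, among others, "All nurse (including nursing assistant) to patient", the mental health and comprehensive nurse-to-patient ratios, the mental health to comprehensive ratio, and nursing hours per patient day built on the day's nurse total. Section 2.12 also takes the day's total nurse count as a denominator.

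**The concern.** Education is missing for an identifiable group, known in advance, and two of the three branches respond by deleting. The stated reason does not fit the planned outputs. Sections 2.14 and 2.26 say that no association will be tested and no inference made. Several of the descriptive measures need to know only that a nurse was on the ward. A nurse who worked the shift but is deleted drops out of a total that should include that nurse.

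The third branch helps little. Imputation would keep the nurse in the count, but the Limitations say that gender, age, experience and contract type are not extracted. Since education is unrecorded for agency nurses as a group, imputed values could only borrow the permanent-staff mix, perhaps by shift. These data cannot check that assumption.

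The study exists to learn whether skill mix can be measured from administrative data. The share of nurse-shifts with unknown education is a central answer to that question, and no planned summary reports it.

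**Working it through.** **1. Reproduce the protocol's figure.** The example in section 2.25 has 8, 9 and 10 comprehensive and 2, 3 and 4 mental health nurses over three days. The ratio of totals is (8+9+10)/(2+3+4) = 27/9 = 3.00, the stated 3:1. The example's nurse total is 27 + 9 = 36 nurse-days.

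**2. Add agency nurses of unknown education.** The protocol gives no agency share, so I assume *a* = 1, 2 or 3 per day, that is 3*a* over the stay. The true total is 36 + 3*a*; after deletion of nurse records it is 36.

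- All-nurse understatement: 3*a*/(36+3*a*). Nursing hours per patient day fall by the same proportion, because the multiplier and the patient count do not change.
- Mental health nurse-to-patient: between 0 and 3*a*/(9+3*a*), the maximum applying if every unknown is a mental health nurse.
- Comprehensive nurse-to-patient: between 0 and 3*a*/(27+3*a*), the maximum applying if every unknown is a comprehensive nurse.
- Comprehensive to mental health ratio, if all unknowns are registered nurses: from 27/(9+3*a*) to (27+3*a*)/9.

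| *a* per day | True total | All-nurse understated by | Mental health measure, at most | Comprehensive measure, at most | Ratio reported | Ratio could be |
|---|---|---|---|---|---|---|
| 1 | 39 | 3/39 = 7.7% | 3/12 = 25.0% | 3/30 = 10.0% | 3.00 | 2.25–3.33 |
| 2 | 42 | 6/42 = 14.3% | 6/15 = 40.0% | 6/33 = 18.2% | 3.00 | 1.80–3.67 |
| 3 | 45 | 9/45 = 20.0% | 9/18 = 50.0% | 9/36 = 25.0% | 3.00 | 1.50–4.00 |

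The example lists only registered nurses. With enrolled nurses, assistants and students in the total, the same *a* would be a smaller share.

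**3. Special case.** If agency nurses have the same 3:1 mix, the ratio is (27+2.25*a*)/(9+0.75*a*) = 3.0 for every *a*, so it is unbiased. The all-nurse, mental health and comprehensive nurse-to-patient measures still all fall by the agency share.

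**4. The other reading: patient rows are deleted.** Section 2.24 puts the final dataset at patient level, and section 2.23 does not name the unit of deletion. Assume that 30% of days have at least one agency nurse. With independent days, the share of stays lost is 1 − 0.7³ = 66% for three days and 1 − 0.7⁷ = 92% for seven. Agency cover may cluster. Without independence, the loss can be anywhere from 30% to 90% (3 × 30%) for three days, and from 30% to 100% for seven. On this reading the retained patients' headcounts are intact; the harm is loss of patients.

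**The case against.** The best defence is that the reason given for deletion concerns only the association with education. The headcount measures are defined by presence, so an analyst could keep nurses of unknown education in the totals and drop them only from education-based ratios. That is a sensible way to proceed, but the plan does not state it: section 2.23 exempts no measure, and its reason has no application in a study that tests no association.

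Other objections stand in part. Deletion is conditional, since the missing-at-random branch imputes. The extraction form (Table S3) is not shown, and a blank entry could already mark unknown education, so the missing code is weak evidence alone. The Limitations disclose the gap, though as a loss of precision and not as possible bias.

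A reader might infer that every nurse-to-patient measure is undercounted and that the skill-mix ratio is made to look more certain than it is. The documents do not support either. The mental health and comprehensive measures fall only so far as the deleted nurses belong to those categories, and the lower limit is zero. No interval or test is planned, so there is no formal statement of certainty to be wrong. What can be shown is that the ratio may be biased and is reported without bounds.

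**Conclusion.** The point holds in a conditional form. Where education is judged missing completely at random or not at random, the rule as written deletes a group that the protocol knows will lack it.

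- If nurse records go, the all-nurse-to-patient ratio and nursing hours per patient day are understated by exactly the share of nurses with unknown education. The mental health to comprehensive ratio may be biased in either direction.
- If patient rows go, patients with any agency-covered day are lost.

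These harms are alternatives, and the text must say which unit is meant. Every size above rests on an assumed agency share, and the ratio bounds assume that all the unknowns are registered nurses; enrolled nurses or assistants enter neither side of that ratio. The point deserves correction but does not threaten the study, which is descriptive, plans no inference and partly discloses the problem.

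**What to change.** 1. Add a sixth training code for education unknown or agency.
2. State that neither nurse records nor patient rows are deleted because a nurse's education is unknown.
3. Keep these nurses in all total counts, in nursing hours and in the all-nurse-to-patient ratio.
4. Report the percentage of nurse-shifts with unknown education by site, as a feasibility result.
5. Report the mental health to comprehensive ratio on known education, with two bounds: all unknown registered nurses comprehensive, and all mental health.
6. Say in the Limitations that unknown agency education may bias the estimates as well as affect their precision.

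The cost is one code and two further summaries. The ratio will look less precise. No new data on individuals are needed and the design does not change.
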